## **1. INTRODUCTION**

### **1.1. STUDY BACKGROUND**

Hypertension is a major risk factor for heart attacks and stroke. Primary hyperaldosteronism (PHA) is an important cause of hypertension and is characterised by excessive aldosterone production by one or both adrenal glands. PHA carries significant cardiometabolic risk over and above that conferred by elevated blood pressure alone. Stroke, myocardial infarction and atrial fibrillation are increased 4 to 12 fold compared to age, gender and blood pressure-matched subjects with essential hypertension.

Detection rates of PHA have improved, largely due to greater availability of high throughput renin assays. However, in current UK clinical practice, only a tiny proportion of patients with PHA complete the investigational pathway and are referred for potentially curative surgery.

One of the main barriers is the difficulty of proving that only one adrenal gland is the culprit. The test widely considered to be most accurate in distinguishing unilateral (surgically-treated) from bilateral (managed medically) disease is adrenal venous sampling (AVS). This diagnostic procedure is difficult, time-consuming, invasive, available in only a few centres, and has variable success rates, depending on technical expertise and the diagnostic criteria employed.

A non-randomised proof-of-concept study showed that 11C-metomidate PET CT scanning is comparable to AVS in distinguishing unilateral from bilateral PHA. Since then, considerable clinical experience with 11C-metomidate PET-CT scanning has accumulated, although robust data are lacking to endorse its widespread use as the investigation of choice.

### **1.2. STUDY OBJECTIVES**

#### **1.2.1. PRIMARY OBJECTIVE**

To determine whether 11C-metomidate PET-CT is superior to adrenal vein sampling in diagnosing unilateral PA, by measuring normalisation of aldosterone/renin ratio and potassium, and change in blood pressure, following adrenalectomy.

#### **1.2.2. SECONDARY OBJECTIVES**

The secondary objectives as listed in the protocol are:

- To investigate whether outcomes differ between those patients who progress to surgery on the basis of PET-CT and/or AVS results, and those patients who do not.

- To investigate whether measurements during 11C-metomidate PET-CT or AVS improve prediction of outcome after surgery.
- To investigate whether blood pressure response to therapy with spironolactone/eplerenone predicts outcome after surgery.
- To investigate whether demographic, genotypic, and pathological data, improve prediction of outcome after surgery.

### **1.2.3. ASSESSMENT OF EFFICACY AND SAFETY**

Efficacy will be determined from measurements of Aldosterone Renin Ratio (ARR), Potassium, Blood Pressure (BP), and BP medication, each at baseline and following treatment. Differences in outcome between those who undergo surgery on the basis of either 11C-metomidate PET-CT or AVS, but not both, will be used to compare performance.

Safety will be assessed by monitoring symptoms, BP, renal function and serious adverse events at each visit.

### **1.3. STUDY DESIGN**

This is an observational multi-centre prospective cohort study.

### **1.4. RANDOMISATION**

The order in which diagnostic tests were to be applied was randomised, but this was not always logistically feasible. Where applicable, data may be summarised in relation to the randomised order of the tests, or the order in which the tests were received.

### **1.5. SAMPLE SIZE AND POWER**

The original sample size calculations carried out at the design stage are reported in section 33.0 of the study protocol, and is reproduced below:

The table below shows potential outcomes from the two separate investigations in patients recruited to MATCH:

| Diagnostic Tests |                | Normalisation of plasma renin & aldosterone/renin ratio after surgery (i.e. confirmed unilateral PHA) |            |
|------------------|----------------|-------------------------------------------------------------------------------------------------------|------------|
| AVS              | PET-CT         | No                                                                                                    | Yes        |
| Unsuccessful     | Bilateral      | A (=9%)                                                                                               | B (=0%)    |
| Unsuccessful     | Unilateral     | C (=1%)                                                                                               | D (=10%)   |
| Bilateral        | Bilateral      | E (=35%)                                                                                              | F (=0%)    |
| Bilateral        | Unilateral     | G (=1%)                                                                                               | H (=9%)    |
| Unilateral       | Bilateral      | I (=0.5%)                                                                                             | J (=3.5%)  |
| Unilateral (c)   | Unilateral     | K (=1%)                                                                                               | L (=29%)   |
| Unilateral (d)   | Unilateral     | M (=0.25%)                                                                                            | O (=0.25%) |
| Unilateral       | Unilateral (d) | P (=0.25%)                                                                                            | Q (=0.25%) |

Key: c = concordant; D = discordant (i.e. PET-CT and AVS lateralise to opposite sides)

The accuracy of PET CT will be estimated in patients having surgery, given by:

$$(D+H+I+L+O+Q) / n$$

The accuracy of AVS will be estimated by  $(G+J+L+M+P) / n$

A test of whether these accuracies differ will therefore be a test of whether

$$(D+H+I+L+O+Q) = (G+J+L+M+P)$$

or whether

$$(D+H+I+O+Q) = (G+J+M+P)$$

This can be achieved by a one sample binomial test of whether

$$p = (D+H+I+O+Q) / (D+H+I+G+J+M+O+P+Q) = 50\%$$

Given the estimated proportions given above, the anticipated value of  $p$  is 80%. To have 90% power at a 1% significance level to show that  $p$  is different to 50%, assuming the true value of  $p$  to be 80%, we require the number of participants in the subgroup  $(A+D+H+I+G+J+M+O+P+Q)$  to be 32 (based on an exact binomial test). Since this subgroup is an estimated 25% of the study population, we would need to recruit 128 participants. Assuming missing data of 10% of people recruited, our target recruitment will be 140.

## 1.6. INTERIM ANALYSIS AND STOPPING RULES

Not applicable.

## 1.7. STUDY POPULATION

The full list of inclusion and exclusion criteria are given in the study protocol, section 10.0.

## **1.8. OUTCOMES**

Outcomes for statistical analysis will be assessed at 6 months after surgery, or 9-12 months after MDT decision, in those who do not undergo surgery. These time points are considered equivalent, occurring at approximately the same time since baseline. Where follow-up data is not available at this time point, data from a later visit (up to 12 months) will be used; if this is not available, an earlier visit (closest available) will be used.

Outcomes for statistical analysis will be referred to as collected “at 6 months” throughout this SAP.

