## **20.0 Study Outcomes**

### **20.1 Primary Outcome(s)**

1. Change in ARR from baseline to 6 months after surgery, or 9-12 months after MDT in patients not proceeding to surgery. (For patients whose surgery takes place less than six months prior to overall study-end, data will be used from the 3 month post-op visit, or the six-month visit will be brought forward. This qualification applies to all other reference to the six-month visit and data in this protocol.)
2. Change in SBP (mean of at least 12 measurements from 3 days home monitoring), from baseline to 6 months after treatment, or 9-12 months after MDT in patients not proceeding to surgery

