### **1.9. PASO CRITERIA**

The following criteria will be used to define cure of hypertension, from the PASO criteria [Williams TA, et al. Lancet Diabetes Endocrinol. 2017 Sep; 5(9): 689-699], six months post-adrenalectomy.

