### **2.2.6. WEEK 4**

The following information collected at 4 weeks will be summarised for all participants in the Full Analysis Set, as a whole and according to whether the participant later underwent surgical treatment:

- Medications
  - Number of different classes of antihypertensive medications being used, and whether using each class of medication
  - Total defined daily doses of antihypertensive medications being used, and defined daily doses of each class of medication
- Clinic readings of systolic blood pressure, diastolic blood pressure, heart rate
- Home readings of systolic blood pressure, diastolic blood pressure, heart rate
- Blood biomarkers
  - Sodium, potassium, creatinine, eGFR, urea, bicarbonate

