## **2.3. EFFICACY OUTCOMES**

### **2.3.1. PRIMARY OUTCOMES**

The primary outcomes will be analysed hierarchically. If the first primary analysis is statistically significant at  $p < 0.05$ , then the second primary outcome will be analysed; if the second primary analysis is statistically significant at  $p < 0.05$ , then the second primary outcome will be analysed; and so on. If any primary analysis fails to reach  $p < 0.05$ , then subsequent analyses will be considered secondary analyses.

Each primary outcome will be analysed in the subgroup of FAS patients who undergo surgery.

- Cure of hypertension at 6 months (non-inferiority analyses)
  - comparing accuracy of AVS and 11C-Metomidate PET-CT
  - each scan judged to be accurate if it indicated unilateral disease and cure of hypertension was achieved after surgery, or if the scan did not indicate unilateral disease and cure was not achieved after surgery
  - report estimated difference in accuracy (Newcombe-Wilson method for paired data) between 11C-Metomidate PET-CT and AVS, with 95% CI
  - non inferiority of 11C-Metomidate PET-CT will be declared if the lower limit of the above 95% CI is greater than -17%
  - each measure of cure (see Section 1.8) will be analysed in turn
- Cure of hypertension at 6 months (superiority analyses)
  - in addition to above, report p-value from exact McNemar test
  - superiority of 11C-Metomidate PET-CT will be declared if  $p < 0.05$ , and the lower limit of the 95% CI is greater than 0%

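### SAP 1.8 names no earliest visit that may replace a missing 6-month outcome, so a 4-week post-operative result can be scored as the 6-month result in the primary accuracy comparison

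*Combined protocol and SAP*

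**What the plan says.** **The rule.** SAP 1.8 states: "Outcomes for statistical analysis will be assessed at 6 months after surgery, or 9-12 months after MDT decision" in those not operated on. If that visit is missing, "data from a later visit (up to 12 months) will be used", and "if this is not available, an earlier visit (closest available) will be used". Whichever visit supplies the value, the rest of the SAP calls it the 6-month outcome.

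**Where it is used.** SAP 2.3.1: "Each primary outcome will be analysed in the subgroup of FAS patients who undergo surgery". It goes on: "each scan judged to be accurate if it indicated unilateral disease and cure of hypertension was achieved after surgery", or if the test did not indicate unilateral disease and surgery did not bring cure. SAP 1.9 applies the cure criteria "six months post-adrenalectomy".

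**The protocol's own exception.** Protocol 20.1 covers only patients operated on less than six months before study end. For them, "data will be used from the 3 month post-op visit, or the six-month visit will be brought forward".

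**What the visits collect.** The 4-week and 3-month post-operative visits (SAP 2.2.9, 2.2.10) record BP, medication, potassium, renin, aldosterone and ARR. The pre-surgical visits at weeks 2 and 4 of spironolactone/eplerenone (SAP 2.2.5, 2.2.6) record BP and medication, but the blood tests are only "Sodium, potassium, creatinine, eGFR, urea, bicarbonate".

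**The concern.** The fallback has no lower bound, and it feeds the primary endpoint. For an operated patient with nothing at 6 or 12 months and no 3-month visit, the rule as written takes the 4-week post-operative visit and reports it as a 6-month result. Neither document says how a 4-week result relates to a 6-month one, so the direction of any error is unknown.

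Some use of the rule is likely. The protocol synopsis says operated patients will attend as many visits as fit before study end, and protocol 20.1 expects some to lack a 6-month visit.

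A wrong cure status matters most where the two tests disagree, because it moves the patient from one discordant cell of the paired table to the other. Superiority in SAP 2.3.1 rests on those cells through the exact McNemar test. The hierarchy also requires p<0.05 at each step, so losing significance on the first outcome would make the later ones secondary.

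The same sentence governs patients who are not operated on. Between baseline and their visit at 9-12 months after the MDT, their only scheduled visits are weeks 2 and 4 of spironolactone/eplerenone. A literal fallback for them is a reading during the drug test, or baseline. That affects the secondary comparison of surgery with no surgery in SAP 2.3.2.

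**Working it through.** The plan states no figure for this rule, so there is none to reproduce. The check has two parts.

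**1. The sections side by side**

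| Question | Protocol 20.1 | SAP 1.8 |
|---|---|---|
| Who may have an early substitute? | Surgery less than six months before study end | Anyone without 6-month or later data |
| Which visit? | 3-month post-operative, or a brought-forward 6-month visit | Closest earlier visit |
| Earliest visit named? | Yes | No |
| Restricted to post-operative visits? | Yes | Not stated |

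SAP 1.10.4 lists two departures from the protocol (CETO analyses left to a separate plan; PASO-based primary outcomes) and not this one. SAP 2.3.6 plans one sensitivity analysis, excluding AVS technical failures.

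**2. Illustration of size**

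Assumptions: 70 operated patients (the minimum in protocol 12.1); the proportions in protocol 33.0 and SAP 1.5; every patient with a unilateral result is operated on; normalisation in that table is taken as cure.

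- Operated share: C+D+G+H+I+J+K+L+M+O+P+Q = 56% of recruits.
- Only PET-CT accurate: D+H+I = 10+9+0.5 = 19.5; 19.5/56 × 70 = 24.4, taken as 24.
- Only AVS accurate: C+G+J = 1+1+3.5 = 5.5; 5.5/56 × 70 = 6.9, taken as 7.
- Both accurate: L+O+Q = 29.5; 29.5/56 × 70 = 36.9, taken as 37.
- Neither accurate: K+M+P = 1.5; 1.5/56 × 70 = 1.9, taken as 2.

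Patients whose tests point to opposite sides get the same score for both tests, because SAP 2.3.1 does not use the side. The difference is (24−7)/70 = +24.3 points.

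Now let *k* cured patients with a unilateral result on PET-CT only be mis-scored as not cured. Each moves the difference by 2/70 = 2.9 points. With the SAP's own methods (Newcombe-Wilson paired interval, exact McNemar test):

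| k | Only PET-CT / only AVS accurate | Difference (points) | 95% CI | p |
|---|---|---|---|---|
| 0 | 24 / 7 | +24.3 | 9.2 to 38.0 | 0.003 |
| 1 | 23 / 8 | +21.4 | 6.2 to 35.5 | 0.011 |
| 2 | 22 / 9 | +18.6 | 3.2 to 32.9 | 0.029 |
| 3 | 21 / 10 | +15.7 | 0.2 to 30.2 | 0.071 |
| 6 | 18 / 13 | +7.1 | −8.4 to 22.2 | 0.47 |
| 9 | 15 / 16 | −1.4 | −16.8 to 14.0 | 1 |
| 10 | 14 / 17 | −4.3 | −19.5 to 11.2 | 0.72 |

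At k=3 the lower limit is still just above zero, but p exceeds 0.05 and superiority requires both.

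The table takes the worst direction. If the affected patients are instead a random share of all operated patients and each is scored not cured:

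- Unaffected difference: (19.5−5.5)/56 = +25.0 points.
- Difference if everyone were scored not cured: PET-CT is then right in I+J = 4 and AVS in C+D+G+H = 21, so (4−21)/56 = −30.4 points.
- Cost per affected patient: (25.0+30.4)/70 = 0.8 points. Seven of 70 would bring +25.0 to +19.5.

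With the synopsis figure of 90 operated patients, the steps become 2/90 = 2.2 points in the worst direction and 55.4/90 = 0.6 points at random.

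**The case against.** The best defence is that the SAP must be read as a whole. Accuracy is scored on cure after surgery (2.3.1), the criteria apply at six months post-adrenalectomy (1.9), and SAP 1.8 concerns missing follow-up data. Baseline is the reference for change, and no section allows it to serve as outcome. A later visit is tried first, and both early post-operative visits collect everything needed. A pre-operative visit would be reached only by an operated patient with nothing usable at 4 weeks, 3, 6 or 12 months. Even then, weeks 2 and 4 carry no renin or aldosterone, so the two biochemical outcomes that open the hierarchy could not be scored from them. Complete clinical success could not be met by a patient taking spironolactone/eplerenone.

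This stands. A reader might infer from SAP 1.8 that primary accuracy will be scored on pre-operative data, or that the baseline value becomes the biochemical outcome. The documents do not support either; the most that can be said is that the wording does not rule out a pre-operative visit.

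A reader might also set 2.9 points per patient against the 17-point margin and conclude that six mis-scored patients use it up. They do not: the margin is compared with the lower confidence limit, the planned difference starts at about +24, and six leave that limit at −8.4. Nor does the protocol's 10% help, since it refers to withdrawals or missing data among recruits, not to missing 6-month visits.

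The defence does not answer the 4-week visit, which is after surgery and has all the measurements. SAP 1.10.2 promises summaries with and without carried-forward values, not a repeated primary test. SAP section 3 leaves missing-data rules to a separate validation plan, which was not supplied. That plan might set a bound, but the operative rule in SAP 1.8 has none.

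**Conclusion.** The concern holds as an unbounded and ambiguous fallback in the primary endpoint. As written, SAP 1.8 allows a 4-week post-operative result to be analysed as the 6-month outcome. It is wider than protocol 20.1, is not declared as a deviation, and no planned analysis would show its effect. It also leaves patients who are not operated on with no scheduled substitute except the drug-test visits or baseline.

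The size is conditional, because neither document says how many 6-month visits will be missing or how often an early visit would give the wrong status. Under the planning proportions with 70 operated patients, three errors all running against PET-CT would be enough to lose superiority, the primary objective in SAP 1.2.1. Non-inferiority is robust, failing only at ten such errors, and randomly spread errors do far less harm.

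**What to change.** Amend SAP 1.8 before database lock:

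- For operated patients, only post-operative visits qualify, with the 3-month visit as the earliest substitute. If there is none, the outcome is missing.
- For patients not operated on, baseline and the week 2 and week 4 visits are not used as the outcome.
- Reconcile the wording with SAP 1.9 and 2.3.1 and with protocol 20.1. The protocol allows the 3-month visit only for surgery near study end, so wider use still has to be listed in SAP 1.10.4 or put into the planned protocol amendment.
- Add to SAP 2.3.6 a repeat of the primary analysis using only in-window 6-month data, and state the width of that window.
- Report how many patients have a substitute visit, by visit used and by which test indicated surgery.

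The cost is a short change of wording and one extra analysis. A few patients will become missing who would otherwise have had a substituted value.

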### **1.8.1. PRIMARY OUTCOME**

The following outcomes will be considered as primary outcomes. These outcomes relate to cure of hypertension at 6 months. Definitions of biochemical and clinical success according to the PASO criteria will be used (see Section 1.9). These will be analysed hierarchically, with each analysis being considered as part of the primary analysis if all preceding analyses demonstrate statistical significance at  $p < 0.05$ . Otherwise, analyses of subsequent outcomes will be considered to be secondary analyses.

- At least partial biochemical success
- Complete biochemical success
- At least partial clinical success
- Complete clinical success

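### The primary hierarchy advances on p < 0.05 without naming a hypothesis or direction, and the only p-value defined belongs to the superiority test

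*Combined protocol and SAP*

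**What the plan says.** SAP 1.8.1 lists four outcomes in order: at least partial biochemical success, complete biochemical success, at least partial clinical success, complete clinical success. The rule for moving down is "These will be analysed hierarchically, with each analysis being considered as part of the primary analysis if all preceding analyses demonstrate statistical significance at" (the threshold given is p < 0.05). Section 2.3.1 repeats it ("If the first primary analysis is statistically significant at" that level, the next outcome is taken) and sends anything after a failure to secondary status.

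Section 2.3.1 then sets two decisions per outcome, in the FAS patients who have surgery:

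- **Non-inferiority.** "report estimated difference in accuracy (Newcombe-Wilson method for paired data) between 11C-Metomidate PET-CT and AVS, with 95% CI". Then "non inferiority of 11C-Metomidate PET-CT will be declared if the lower limit of the above 95% CI is greater than -17" per cent. No p-value is attached.
- **Superiority.** "in addition to above, report p-value from exact McNemar test". It is declared if p < 0.05 "and the lower limit of the 95% CI is greater than 0" per cent.

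The requirement that the result favour PET-CT belongs to the superiority declaration. Neither statement of the gate repeats it. The SAP does not say whether a met non-inferiority limit counts as significance, and it does not state the sidedness of the McNemar test. The general p-value convention in SAP 1.10.2 concerns independent-samples comparisons, so it does not supply a p-value for this paired analysis.

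**The concern.** Non-inferiority is listed first for each outcome but produces no p-value, while the gate needs one. Taken at its word, the rule can go wrong in two ways:

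- PET-CT meets non-inferiority on outcome 1, the McNemar test is not significant, and every later non-inferiority result becomes secondary.
- PET-CT is significantly less accurate than AVS on outcome 1 and fails non-inferiority, yet p < 0.05, so outcome 2 keeps primary status.

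What is at stake is the confirmatory label on outcomes 2 to 4. Complete biochemical success, the outcome nearest to the normalised renin and ARR used in protocol section 33 to define confirmed unilateral disease, is second in the list. If the SAP does not settle the rule, its status depends on a reading that could be chosen after the data are seen.

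**Working it through.** **Inputs.** Operated patients: 70 (protocol section 23) or 90 (synopsis). Margin 17 points, 95% Newcombe paired interval and exact McNemar test: SAP 2.3.1. From the cell table in protocol section 33 (repeated in SAP 1.5):

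- PET-CT alone correct: D+H+I+O+Q = 10+9+0.5+0.25+0.25 = 20%.
- AVS alone correct: G+J+M+P = 1+3.5+0.25+0.25 = 5%.
- At least one test unilateral, so surgery is offered: C+D+G+H+I+J+K+L+M+O+P+Q = 56%.

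The stated p = 80% reproduces: 20/25. Discordance among surgical patients is 25/56 = 44.6%. The lower discordance of 20% and the 10% with both tests wrong are assumptions. The 32 discordant patients required in section 33 play no part here.

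**Two worked datasets, n = 70.** Let b = PET-CT only correct, c = AVS only correct, d = both wrong, a = the rest. McNemar p = 2 × P(X ≤ min(b,c)), X ~ Bin(b+c, 0.5), capped at 1. Newcombe lower limit = Δ − √[(p₁−l₁)² − 2φ(p₁−l₁)(u₂−p₂) + (u₂−p₂)²], where p₁ and p₂ are the PET-CT and AVS accuracies, l and u are Wilson limits, and φ is the continuity-corrected correlation.

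1. a=47, b=8, c=8, d=7. p₁ = p₂ = 55/70 = 0.786; Wilson 0.676 to 0.866; φ = (47×7 − 8×8 − 35)/825 = 0.279. The half-width is √(0.1096² − 2×0.279×0.1096×0.0799 + 0.0799²) = 0.116. The difference is 0, 95% CI -11.6% to +11.6%; p = 1.00. **Non-inferiority met, gate closed.**
2. a=45, b=4, c=14, d=7. Difference 49/70 − 59/70 = -14.3%, 95% CI -25.9% to -2.4%. p = 2 × (1+18+153+816+3060)/2¹⁸ = 8096/262144 = 0.031. **Non-inferiority failed, AVS significantly better, gate open.** At n = 90 with the same 4 versus 14 and d = 9, the interval is -20.5% to -1.8% and p is again 0.031.

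**How often.** For discordance δ and true difference Δ, the cell probabilities are (δ+Δ)/2 for PET-CT only, (δ−Δ)/2 for AVS only, 0.10 for both wrong, and the remainder for both right. I summed multinomial probabilities over all tables, taking the gate as two-sided McNemar p < 0.05. Results for n = 70:

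| True Δ | δ | NI met | Gate open | NI met, gate closed | NI failed, gate open |
|---|---|---|---|---|---|
| 0 | 20% | 87% | 2.6% | 85% | 1.3% |
| 0 | 44.6% | 58% | 3.1% | 57% | 1.6% |
| -17 points | 20% | 2.6% | 92% | 2.3% | 91% |
| -17 points | 44.6% | 2.7% | 50% | 2.7% | 50% |

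In the last two rows virtually every open gate favours AVS. At n = 90, non-inferiority met with the gate closed is 67–92% at equal accuracy, and the gate open after failed non-inferiority is 63–96% at -17 points. Dropping the continuity correction gives 57–87% in place of 57–85%. Using 5% both wrong moves those figures by less than one point.

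**Under the design's effect** (δ = 44.6%, 80% of discordant pairs favouring PET-CT), the gate opens in 91.9% of trials at n = 70 and 97.3% at n = 90, always in favour of PET-CT for practical purposes.

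**The case against.** The strongest reply is that the gate speaks of a significant primary analysis, and a lower 95% limit above the margin is a significant non-inferiority result at one-sided 2.5%. A gate based on the confidence limit may therefore be what was meant. That stands as far as it goes: a reader might infer that the plan forbids non-inferiority from ever advancing the sequence, and the documents do not support so firm a statement. What they support is that the SAP does not say so, and that its only defined p-value points elsewhere.

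Second, two-sidedness is inferred. If the test were one-sided for PET-CT, the AVS route would vanish. But the added requirement of a lower limit above zero would then be largely redundant, so two-sided is the likelier reading.

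Third, the harm is bounded. An AVS-favouring result cannot be declared PET-CT superiority, later outcomes must still pass their own rules, and a closed gate relabels results without suppressing them. The outcomes do have an order, since "each measure of cure (see Section 1.8) will be analysed in turn". The primary objective in SAP 1.2.1 is superiority, and under the design's effect the gate usually opens. All of this stands and limits the size of the point.

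Two stronger inferences fail. A reader might take the roughly 97% of equal-accuracy trials with a closed gate as the share in which a non-inferiority result is demoted. That count includes trials where non-inferiority failed on outcome 1, which would stop any sensible sequence; the relevant share is 57–85%, and a demotion also needs non-inferiority on the later outcome. A reader might also infer that separate non-inferiority and superiority sequences would lose family-wise control. Two fixed sequences at one-sided 2.5% each are bounded by 2.5% + 2.5% = 5%, and 0.05 is the only level that the SAP states for the hierarchy.

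**Conclusion.** The point holds in this form: the gate names neither hypothesis nor direction and, applied literally, gives the wrong primary or secondary status in both directions. With 70 operated, at equal accuracy non-inferiority on outcome 1 is met while the gate stays closed in about 57–85% of trials. With PET-CT truly 17 points worse, the gate opens in favour of AVS despite failed non-inferiority in about 50–91%. These figures rest on a two-sided McNemar test, 10% of patients with both tests wrong and discordance from 20% (assumed) to 44.6% (from the cell table, here combined with differences that the table does not assume). If the design's 80% holds, the gate opens about 92% of the time and little is lost. The defect matters when PET-CT is similar to or worse than AVS, where the status of a non-inferiority claim matters most.

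**What to change.** Replace the gate wording in SAP 1.8.1 and 2.3.1 with one paragraph:

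1. The non-inferiority sequence moves through the four outcomes in the listed order, and only while the lower 95% limit exceeds -17%.
2. Superiority follows the same outcome order. Each outcome is tested only after its own non-inferiority has been shown and all earlier superiority tests have succeeded. It requires two-sided exact McNemar p < 0.05 and a lower 95% limit above 0. Pairing the tests by outcome matters: if superiority waited for the whole non-inferiority sequence, failure on complete clinical success would block superiority on the first biochemical outcome.
3. Each sequence runs at one-sided 2.5%, so the two together are bounded by 5%.
4. Results after a failure in a sequence are labelled secondary for that sequence. Correct the sentence in 2.3.1 that names the second outcome twice where the third is evidently meant.

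The cost is one paragraph, to be settled before database lock. It needs no new data, patients or procedures.
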